### Sample size determination and power

The sample size of 42 is primarily calculated to test consistency with desired primary outcome effect size. Following Cocks and Torgerson [45], a sample size sufficient to reject a lower limit for the effect size of 0 is estimated (assuming one sided *α* = 0.05, 1− *β* = .80). Assuming sd = 7 in the SDQ is representative, with a lower limit = 2 for meaningful clinical change, the effect size = .29. For a feasibility trial, to reject an effect size of 0 a sample size of 32 (16 in each arm) is required, or 42 children (21 per arm) allowing for 30% drop out.

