### Aim 6: likely effect size of the intervention

The preliminary effect size estimated for this study is based on an assumed minimum difference in the SDQ of 2 points given an sd = 7 typical of this sample of children. This gives a conservative estimate for an effect size of .29, and the sample size is estimated to enable a lower limit of 0 to be rejected. The analysis will seek to estimate the effect size from the observed data, with an estimated lower limit as suggested by Cocks and Torgerson [45].

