The wide-ranging challenges involved in the present research mean that a feasibility study is the most useful design. The overall research question aims to identify the most cost-effective treatment strategy for these children and incorporates a range of measures to identify the intervention with the greatest potential for positive impact on emotional health and well-being. By testing the feasibility of a trial to answer this research question, our study contributes information of major importance to the NHS. Potential challenges or difficulties to completing a larger-scale trial would allow us to modify and improve our research protocol, or if necessary to not proceed, if the findings of the feasibility study suggested that this intervention does not have a significant chance of improving outcomes for users of the NHS. Our hypothesis is that the outcomes will be better with MBT than UCC for equivalent cost. Given the current effect estimate, for roughly every eight families seen, at least one more family would benefit with MBT than with UCC, giving a saving to public services of up to £15,382 per family per year (minus the £2000 cost of treatment). These savings are of course in addition to the benefit of helping more families with the distress of relational difficulties and emotional and behavioural challenges.

The study could improve the stability of foster placements and the relationships between individuals within foster families, including a strengthened sense of security and belonging for CLA. This study therefore has the potential for direct impact on the day-to-day practice of health service staff, to bring savings to the NHS and local authorities, education and criminal justice sectors and benefits for some of the most vulnerable users of the NHS in England.

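### The sample size is said to test consistency with a 2-point SDQ benefit, but the only confidence limit planned is a lower one judged against 0, which does not answer that question

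*Protocol article*

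**What the plan says.** The section on sample size determination and power opens with the purpose: "The sample size of 42 is primarily calculated to test consistency with desired primary outcome effect size". It fixes that effect "with a lower limit = 2 for meaningful clinical change, the effect size = .29", with the SD taken as 7.

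The criterion used for sizing is a different one: "a sample size sufficient to reject a lower limit for the effect size of 0 is estimated", "assuming one sided *α* = 0.05" and with 80% power. The result is that "to reject an effect size of 0 a sample size of 32 (16 in each arm) is required", raised to 42 for drop-out.

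Aim 6 repeats the criterion of rejecting 0. It plans to estimate the effect size from the observed data, "with an estimated lower limit". No section plans an upper limit or compares an interval with 2 points.

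The Discussion allows for not proceeding "if the findings of the feasibility study suggested that this intervention does not have a significant chance of improving outcomes". The section on evaluating the feasibility of a full-scale trial ties the decision to the evaluation of every aim, so Aim 6 is included, but it sets no effect-size threshold.

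**The concern.** Two questions are treated as one. Whether the data are consistent with a 2-point benefit depends on whether 2 lies inside the interval. For a treatment that may fall short, that means asking whether the upper limit, in the direction of benefit, reaches 2. Whether the data reject 0 depends on the lower limit. The article states the first purpose and fixes the criterion for the second.

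The Discussion's reason not to proceed raises the same issue. If benefit is judged against the plan's own 2 points, that reason also needs the upper limit. With a sample this small, a lower limit below 0 is the expected result even when the desired effect is real. A report built around that limit invites readers to see a negative finding where nothing worthwhile has been excluded.

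**Working it through.** **Inputs**, all from the sample size section: SD 7, desired difference 2 points, 16 evaluable per arm, one-sided α 0.05, power 0.80.

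**The plan's own figure.**
- With α and power as written, n per arm = 2(1.645 + 0.842)² / d². This gives 152 per arm (304 in total) at d = 2/7 and 148 per arm (296) at d = .29, not 32.
- If .80 is read as a one-sided confidence level and α is not used, n per arm = 2(0.842 / d)². The totals are 36 at d = 2/7, 34 at d = .29 and 32 at d = .30. This is the reading that comes closest.

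The level of the planned limit is therefore uncertain, and both levels are carried through below.

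**Half-widths with 16 per arm.** SE = 7 × √(2/16) = 2.475 points.
- One-sided 95%: t(30) = 1.697, so 1.697 × 2.475 = 4.20 points.
- One-sided 80%: t(30) = 0.854, so 0.854 × 2.475 = 2.11 points.

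**What each limit shows (SD fixed at 7).**

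| | One-sided 95% | One-sided 80% |
|---|---|---|
| Lower limit if the observed benefit is exactly 2 | 2 − 4.20 = −2.20 | 2 − 2.11 = −0.11 |
| Lower limit clears 0 if the observed benefit exceeds | 4.20 | 2.11 |
| Upper limit falls below 2 if the observed benefit is below | −2.20 | −0.11 |

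Between the last two rows, 0 is not rejected and 2 points is not excluded.

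**How often that happens if the true benefit is 2 points.**
- At 95%: P(lower limit > 0) = 0.196 (t) and P(upper limit < 2) = 0.05, leaving 1 − 0.196 − 0.05 = 0.754.
- At 80%: P(lower limit > 0) = 0.485 (t; 0.487 by normal approximation) and P(upper limit < 2) = 0.20, leaving about 0.31.
- If all 21 per arm were evaluable (normal approximation): 1 − 0.236 − 0.05 = 0.714 at 95% and 1 − 0.534 − 0.20 = 0.266 at 80%.

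**What the upper limit can do at this size.** If the true effect is 0, by symmetry it falls below 2 in about 20% of trials at 95% and about 48% at 80%. A treatment with no effect would therefore still be called consistent with 2 points in about 80% or 52% of trials.

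**The case against.** Several points on the other side are sound.

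- **The estimate is also planned.** Aim 6 gives an effect estimate as well as the lower limit. For a symmetric interval, a careful reader could recover the upper limit by reflection. It would be wrong to infer that the report will contain only a lower limit.
- **No rule reads the lower limit as failure.** A reader might infer that a result exactly on the desired effect would stop the programme. The feasibility section names training, drop-out and completion and sets no effect threshold, so the article does not support that.
- **The Discussion names no 2-point threshold.** Its sentence is loosely worded and could refer to any benefit, or to a judgement across all the findings. The link to the upper limit holds only if benefit is judged against the plan's own 2 points.
- **The size depends on the confidence level.** The 75% belongs to one-sided 95% and falls to about 31% at one-sided 80%. The 75% should not be quoted alone.
- **Overlap with power.** P(lower limit > 0) is the power of the superiority test, so much of the 75% reflects low power. The mismatch is still a separate fault: a larger sample would not make a lower limit against 0 a test of consistency with 2.
- **Reporting detail.** Printing a second limit is often left to an analysis plan. Here, however, the article itself states a purpose and fixes a criterion that does not serve it.

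**Conclusion.** The point holds as a mismatch between stated purpose and stated criterion. Sizing is described as a test of consistency with 2 SDQ points, but the limit planned is a lower one read against 0, and it does not show whether 2 points has been excluded. The consequence is a misleading basis for the decision to proceed, not a faulty formal stopping rule.

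If the desired effect is real, the planned limit would leave 0 unrejected with 2 points still plausible in about 75% of trials (one-sided 95%) or about 31% (one-sided 80%). These figures assume SD 7, 16 evaluable per arm, normally distributed outcomes and an unadjusted comparison of means. The conclusion about which limit answers the question depends on none of these, nor on the cited methods paper, which was not available.

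**What to change.** 1. In Aim 6, report the mean SDQ difference in points with both limits at a stated confidence level. Judge consistency with the desired effect by whether the upper limit, in the direction of benefit, reaches 2 points.
2. State that a lower limit below 0 is not by itself evidence against proceeding.
3. Reword Aim 6 and the sample size section so that purpose and criterion match. Justify the number by the precision that 16 per arm gives: a one-sided half-width of about 4.2 points at 95% or 2.1 at 80%. This replaces the rejection of 0 as the basis for the sample size, so the number is not left without a rationale.
4. Disclose the weakness: if the true effect is 0, the upper limit falls below 2 in only about 20% of trials at 95% or 48% at 80%. The efficacy data should inform the decision to proceed, not dictate it.

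No extra children or data are needed. The cost is rewording, a choice of confidence level, and an open statement that the efficacy result will often be inconclusive.

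### The stated test (one-sided 5%, 80% power, effect size 0.29) needs about 300 evaluable children, not 32; 16 per arm gives about 20% power

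*Protocol article*

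**What the plan says.** The section on sample size determination and power (Protocol article) describes the total of 42 as calculated primarily for consistency with the desired effect on the primary outcome. Citing a pilot-trial method, it says that "a sample size sufficient to reject a lower limit for the effect size of 0 is estimated", and the bracket that follows gives a one-sided alpha of 0.05 and 1−β of 0.80. The effect size comes from the SDQ: "Assuming sd = 7 in the SDQ is representative, with a lower limit = 2 for meaningful clinical change, the effect size = .29". The section then draws its conclusion: "For a feasibility trial, to reject an effect size of 0 a sample size of 32 (16 in each arm) is required". An allowance for losing 30% of participants raises this to a total of 42, with 21 in each group.

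The section on Aim 6 repeats the basis. It calls 0.29 a conservative estimate and says that "the sample size is estimated to enable a lower limit of 0 to be rejected". It then plans to estimate the effect size with a lower limit as the same pilot-trial source suggests, and names no confidence level for that limit.

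**The concern.** All the inputs of an ordinary power calculation are printed: alpha, sidedness, power, SD, difference and null value. An effect of 0.29 SD is small, and 16 per arm is far fewer than a test with 80% power against zero normally needs for it.

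What is at stake is how Aim 6 will be read. The section on evaluating a full-scale trial says that the decision follows evaluation of each aim, and the Discussion allows for not proceeding if the findings suggest no significant chance of benefit. Someone who believes the power is 80% would treat a lower limit below zero as informative against MBT. If the power is really about 20%, that result is the expected one even when the assumed 2-point benefit is real.

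**Working it through.** **Inputs** (all from the sample size section): difference 2 SDQ points; SD 7; d = 2/7 = 0.286, printed as 0.29; null value 0; one-sided alpha 0.05 (z = 1.645); power 0.80 (z = 0.842); 1:1 allocation; 16 evaluable and 21 randomised per arm.

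**1. Sample size from the stated inputs**

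n per arm = 2(1.645 + 0.842)² / d²

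- d = 0.29: 147.0 (t-based: 148)
- d = 2/7: 151.5 (t-based: 153)

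The total is about 295 to 305 evaluable children, against the stated 32.

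**2. Power at the stated sample size** (noncentral t, unadjusted, one-sided 5%)

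| Per arm | d = 2/7 | d = 0.29 |
|---|---|---|
| 16 | 19.6% | 20.0% |
| 21 (no drop-out) | 23.1% | 23.5% |

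The normal approximation at 16 per arm gives 20.1% and 20.5%.

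**3. What 16 per arm can show**

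- SE of d ≈ √(2/16) = 0.354; in SDQ points, 7 × 0.354 = 2.5.
- With an observed d of 0.29, the one-sided 95% lower limit is 0.29 − 1.645 × 0.354 = −0.29.
- Smallest observed d that rejects zero, using t on 30 df (1.697): 1.697 × 0.354 = 0.60. That is 4.2 points, about twice the assumed difference.
- True effect detectable with 80% power: d = 0.90, or 6.3 points (normal approximation 0.88, or 6.2 points).

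**4. Attempts to reproduce 32**

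| Reading | Total n |
|---|---|
| Two-sided 5%, 80% power | 374–386 |
| One-sided 20%, 80% power | 136–140 |
| One-sided 95% limit, no power term | 130–134 |
| One-sample or paired formula | 74–76 |
| One-sided 80% limit, no power term, d = 2/7 | 36 |
| Same, d = 0.29 | 34 |
| Same, d = 0.30 | 32 |

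The last three rows use n per arm = 2 × 0.842² / d², which is 17.4, 16.8 and 15.7. Only d = 0.30 gives 16 per arm. That criterion amounts to one-sided alpha 0.20, with power of about 49% at the protocol's own effect size.

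**5. Baseline adjustment.** The protocol states no baseline correlation. To reach 80% power at 16 per arm, an analysis of covariance would need one of about 0.94 to 0.95. At assumed correlations of 0.3, 0.5 and 0.7, power is about 21%, 24% and 30%.

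**6. Drop-out.** If 30% of 42 are lost, 42 × 0.70 = 29.4 remain, or 14.7 per arm. The SE is then 7 × √(2/14.7) = 2.6 points and power is about 19%.

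**The case against.** The strongest defence is that 32 is a legitimate pilot-trial figure with the wrong criterion printed beside it. Both sections refer to a published pilot-trial method, and 32 does match a one-sided 80% limit at d = 0.30. Aim 6 plans an estimate with a lower limit, not expressly a 5% test. On that view the defect is a misdescription and the trial is not undersized. This affects the choice of remedy, and it is a good reason not to ask for more children. It does not save the text, because the section prints alpha 0.05 and power 0.80 and the source is not available to supply another criterion. At the protocol's own effect size the 80% limit gives 34 or 36, not 32. The matching lower limit, 0.29 − 0.842 × 0.354 = −0.01, falls just short of excluding zero. That shortfall is a rounding effect and should carry no weight as a second failure.

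Two further points limit the concern:

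- **No fixed efficacy rule.** The itemised considerations for a full trial are training and its costs, drop-out, and completion and attendance. The harm is therefore a risk of misreading; no stated rule makes rejection of zero a condition for proceeding.
- **Baseline adjustment.** It would raise power somewhat, so the four-in-five failure rate applies to an unadjusted analysis. At the assumed correlations above, power still reaches only 30%.

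**Conclusion.** The concern holds. The stated primary basis for the sample size is wrong as written: the inputs require about 295 to 305 evaluable children, roughly nine times 32, and 16 per arm gives about 20% power where 80% is claimed. This rests on the protocol's own SD and difference, 16 completers per arm, an unadjusted comparison of means and independent observations. At the planned 30% loss the power is slightly lower, about 19%. No reading that was tried yields 32 while keeping the printed alpha and power. The size of 42 can be kept for a feasibility trial; what must go is the statement of what it can establish about efficacy.

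**What to change.** Keep 42 and correct the two sections.

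- **Sample size section:** remove the statement that 32 children suffice to reject zero at one-sided 5% with 80% power. Say instead that with 16 completers per arm and SD 7, the SE of the SDQ difference is about 2.5 points, a one-sided 80% limit lies about 0.30 SD (2.1 points) from the estimate, and power to reject zero at one-sided 5% for a true 2-point difference is about 20%. Give the figures for the planned 30% loss as well (14.7 per arm): SE about 2.6 points, 80% limit about 0.31 SD (2.2 points) away, power about 19%. If an 80% limit was the intended criterion, say so and state the effect size used.
- **Aim 6:** delete the claim that the sample size allows a lower limit of zero to be rejected. Name the confidence level of the lower limit, and state that a limit below zero is not in itself evidence against MBT.

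The cost is wording in two places. No extra children, visits or funds are needed. The published justification becomes less favourable, but it will be accurate.

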### Participant selection

A total of 42 CLA and their carers will be recruited from routine referrals to CAMHS targeted team. The CLA team within HPFT is a cross-county service with an annual referral rate of 170 children per year. In 2013/14, 74.6% (*n* = 132) of children referred to the service would have met inclusion criteria for this study. Recruitment is planned for 12 months, suggesting that 32% of eligible children will need to be recruited to the study during the recruitment period. Regular monitoring of study progress will identify potential problems early and allow any corrective action to be taken.

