### Aim 4: feasibility and acceptability of randomisation & research procedures

The primary aim of this evaluation will be to examine data completion and retention across the study once the child has been randomised to a treatment arm. Data completion rates will be documented across all the outcome measures, and by treatment arm, and by time point. The analysis will seek to determine whether data completion falls below 75%, and potential differences between treatment arms, responding groups (children, families, teachers) and by subgroups (sex, age [≤11 or >11]), or any other demographic or clinical factor.

The study allows for a 30% drop out at the last follow-up [44]; and the data will be examined similarly for trends in the drop-out of children and their families. This will be tabulated according to treatment and subgroup as outlined above. Drop-out will be matched (tabulation) to the attendance data and to significant events to determine the extent to which drop out is determined by these factors. Regression models may be evaluated whether these factors are potentially informative and the study sample size allows.

The acceptability of randomisation, as well as other elements of the research design, will also be assessed qualitatively, using the *Experience of Therapy and Research Process Interview.* A thematic analysis [43] will be conducted to identify which elements of the research design were experienced as acceptable or non-acceptable. In addition to the process of randomisation, this will include the assessment burden and the appropriateness of each of the research measures (e.g. whether the parenting measures were felt to be appropriate for the experience of foster carers). This will inform the design if a full clinical trial is undertaken.

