### Evaluating the feasibility of a full scale trial

Principal determinants of whether a full scale trial can be undertaken will follow evaluation of each of the study aims as outlined.

Bringing together all the study data will allow trial feasibility to be considered, including the following:The potential to train therapists to deliver the intervention as envisaged and the costs involved.That the external validity of the study is maximised by ensuring that drop-out from the study is within acceptable limits (30%), or that changes can be convincingly made to the study procedures to allow for improved retention in the study.That the internal reliability of the study data is maintained. Data completion for the study measures, and completion of the therapeutic intervention (attendance) will be evaluated to ensure that the completion rate is good (>75%) and that there are no obvious biases in data completion by any particular subgroup. The qualitative evaluation will be considered in informing particular changes that can be made to maximise the study procedures to improve data completion.

The final report will summarise the data to support clear decision to proceed to a full trial, and to inform development of the study procedures to maximise the quality of the trial design.

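### Forty-two children do not give the required 32 completers at 30% drop-out: they leave about 29, and keep 32 only if drop-out is at most about 24%

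*Protocol article*

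**What the plan says.** The Protocol article, section Sample size determination and power, gives two linked figures. The first is the number needed for analysis: "to reject an effect size of 0 a sample size of 32 (16 in each arm) is required". The second follows directly, as the number to recruit: "or 42 children (21 per arm) allowing for 30% drop out". The section presents 42 as driven mainly by the effect-size check on the primary outcome.

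The section Participant selection fixes the same target: "A total of 42 CLA and their carers will be recruited".

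The 30% is placed in time under Aim 4: "The study allows for a 30% drop out at the last follow-up". It appears again in the section Evaluating the feasibility of a full scale trial, as the acceptable limit for drop-out when deciding whether a full trial can go ahead.

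**The concern.** A drop-out rate is a share of the children randomised. A recruitment target that allows for 30% drop-out should therefore still leave the required number after 30% of that target has been lost. Here it does not.

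What is at stake is the stated basis of the sample size. A reader will take it that the trial still has its 32 children if drop-out reaches 30%, and the same 30% is the retention limit in the feasibility assessment. With 42 randomised, the trial can satisfy that limit and still have fewer completers than its own sample size section says are required. The study is also meant to inform the planning of a definitive trial, where the same slip would cost more children.

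**Working it through.** **Inputs.** Required completers: 32, 16 per arm (Sample size determination and power). Recruitment target: 42, 21 per arm (same section and Participant selection). Drop-out: 30% at the last follow-up (Aim 4). Children referred in 2013/14 who would have met the inclusion criteria: 132 (Participant selection).

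**1. Reproducing the plan's figure.** Multiplying the completers by one plus the drop-out rate gives the stated target exactly:
- total: 32 × 1.30 = 41.6, rounded up to 42
- per arm: 16 × 1.30 = 20.8, rounded up to 21

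**2. The target that keeps 32.** If N are randomised and a share d is lost, N × (1 − d) complete. Setting this to at least 32 with d = 0.30:
- total: 32 / 0.70 = 45.7, rounded up to 46
- per arm: 16 / 0.70 = 22.9, rounded up to 23
- check: 46 × 0.70 = 32.2, which meets 32

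**3. What 42 delivers at 30%.** 42 × 0.70 = 29.4 in total, or 21 × 0.70 = 14.7 per arm. The shortfall is 32 − 29.4 = 2.6, about three children.

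**4. The drop-out that 42 can absorb.** 1 − 32/42 = 10/42 = 23.8%.

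**5. In whole children, out of 42.**

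| Lost | Drop-out | Completers | Within 30%? | At least 32? |
|---|---|---|---|---|
| 10 | 23.8% | 32 | yes | yes |
| 11 | 26.2% | 31 | yes | no |
| 12 | 28.6% | 30 | yes | no |
| 13 | 31.0% | 29 | no | no |

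With 11 or 12 losses the trial is inside its drop-out limit but below its stated requirement.

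**6. Effect on precision.** For a small standardised difference with n per arm, the standard error is about √(2/n):
- n = 16: √(2/16) = 0.354
- n = 14.7 (29.4 in total): √(2/14.7) = 0.369
- n = 14.5 (29 in total): √(2/14.5) = 0.371

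The increase is 0.369/0.354 = 1.04, about 4%. With the plan's SD of 7, the standard error of the SDQ difference goes from 7 × 0.354 = 2.5 points to 7 × 0.369 = 2.6 points.

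**7. Recruitment burden.** 42/132 = 32% of eligible children, as the plan says. Recruiting 46 would need 46/132 = 35%.

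**The case against.** The arithmetic is hard to dispute. No section gives another inflation rule or a lower drop-out rate that would make 42 right. The case on the other side concerns weight and reach, and most of it stands.

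- **The trial is a feasibility study.** Its key outcomes concern whether a large trial can be run, and the treatment outcomes serve effect size and power estimation for that trial. No confirmatory conclusion turns on completers 30 to 32, and a 4% wider standard error hardly changes what can be learnt. This stands, and it keeps the point from being a serious defect. It does not remove it, because the plan itself ties 42 to the effect-size check.
- **The 32 is itself uncertain.** The section also states "assuming one sided *α* = 0.05" with 80% power, SD 7 and a difference of 2. A conventional two-group comparison on those inputs needs 2 × (1.645 + 0.842)² / (2/7)², about 152 per arm. That is a separate question. The present point takes 32 as the plan's own requirement and does not depend on how it was reached.
- **The cause is inferred.** The article prints no formula. The exact match in total and per arm makes multiplication by 1.3 the apparent source, but not a documented one. The shortfall is the same either way.
- **The loss is conditional.** About 29 completers applies if the full 30% is lost, and at 24 weeks. More children may be available at the 12-week assessment.

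A reader might also infer that the 30% limit in Evaluating the feasibility of a full scale trial is wrong and should become 24%. The document does not support that. The section links the limit to external validity and acceptable retention, not to keeping 32 children, and it allows for convincing procedural changes where retention falls short. Tightening it could alter the decision on a full trial because of a slip made elsewhere.

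**Conclusion.** The claim that 42 children allow for 30% drop-out from a required 32 is wrong as written. At 30% loss by the last follow-up, about 29 (29.4) remain. Forty-two give 32 only if drop-out is at most about 24% (23.8%). A target that keeps 32 at 30% loss would be 46 (23 per arm), four more than planned.

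This rests on two assumptions: that 32 is the requirement, as the plan states, and that the 30% is a share of those randomised, which is how drop-out at the last follow-up is normally read.

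The size is modest: about three completers, and a standard error of about 0.37 instead of 0.354. It is a minor to moderate correction of a stated figure. A reader might infer that the trial is too small to go ahead, or that its retention limit is invalid; neither follows. What does follow is that meeting the 30% limit does not guarantee 32 completers.

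**What to change.** Keep the target of 42 and restate the sentence in Sample size determination and power along these lines: *42 children give 32 completers if drop-out is no more than 24%; at 30% drop-out about 29 complete.* Quote the precision of the effect size for about 29 completers (standard error about 0.37) beside the figure for 32 (0.354). Align the sentence under Aim 4 that says the study allows for 30% drop-out.

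Leave the 30% limit in Evaluating the feasibility of a full scale trial unchanged, and add a note there that a trial within this limit may still have fewer than 32 completers.

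The cost is wording only, together with a less favourable stated tolerance. Recruitment opened in April 2016, and this change needs no extra children. Raising the target to 46 would also remove the discrepancy, at the price of four more children and 35% rather than 32% of those eligible, but a gap of this size does not require it.
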